### 4.4.7 Study variables

## Independent/factor:

(i) Routine ANC care available in the health facilities (standard care);

(ii) *Promotional team* giving additional education care to pregnant women with periodic mobile phone reminders.

*Dependent/outcome variables*

1. Timely return ANC visits (return within seven days of the scheduled appointment date)
2. Completion of the four recommended ANC visits
3. Institutional deliveries
4. Newborn care practices:
5. Provision of warmth to the newborn
6. Initiation of breastfeeding within one hour of birth
7. Care for the cord
8. Immunization for the newborn-Polio 0 & 1; BCG within the neonatal period

We will, at the end of the study, assess perceptions of individual women who have participated in this intervention towards the integrated package by administering the tool described by Howie and others ([Howie J, Heaney D et al. 1998](#_ENREF_42)) elaborated in annex 15 (the Patient-Enablement Initiative (PEI).

### 4.4.8 Sample size

Using the formula for cluster randomised trials suggested by Hayes and Bennett ([Hayes and Bennett 1999](#_ENREF_36)),

**n = D(Z_α/2_ + Z_β_)^2^[π_0_(1- π_0_) + π_1_(1- π_1_)]/ (π_0 +_  π_1_)^2^** where

- **n** = number of participants in each arm,
- **D** = the design effect of 2.5,
- **Z_α/2_** = 1.96,
- **Z_β_ = 0.84,**
- **π_0_ =** current rate of institutional deliveries, 23.5%
- **π_1_** = estimated rate of institutional deliveries after the intervention, 33.5%

Substituting in the formula, we obtain a sample size of 788; allowing for a 10% loss-to-follow up we estimate a total population of 868 participants per arm. Further substituting in the formula for required number of cluster, C

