## 4.2.7 Sample size

Preliminary assessments indicate that the staffing level for nurses, midwives and nurse assistants in the two districts could stands at about 200 staffs. The sample size calculation will be estimated using the formulae for cross-sectional studies [$Z^{2}$PQ]/$\delta^{2}$]; substituting the formula-assuming a health worker knowledge of **50%**, with a sampling error of **9%** an estimated sample size of 120 health workers will be recruited. Considering a 10% non response we obtain a sample size of 132 health workers. All midwives working in the two districts, all nurses and nursing assistant in health centres II, III and IV and nurses working in the outpatients and children’s wards will be eligible to participate in the study. A total of 132 health workers from both districts will be randomly selected. A list of all health workers providing services in the two districts will be obtained from their respective health sub districts and stratified by the different cadres (Nursing assistants, nurses and midwives) and a proportionate number will be sampled. For both the quantitative and qualitative studies health workers will be visited in their respective health centres and data will be collected by the Principal Investigator.

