### 4.3.5 Sample size and technique

The formulae for cluster surveys will be used to estimate the maximum number of clusters and sample size. Using the formula,

C= [Z^2^PQ] D/$\delta^{2}b]$ Where,

- Z, the standard normal deviate at 95% confidence which is 1.96
- P, the prevalence of homecare practices in the region taken to be 42% (0.42) [good cord care ([Waiswa P, Stefan P et al. 2010](#_ENREF_99))]
- Q, (1-p) is 0.58
- D, the design effect taken to be 2,
- $\delta$, a sample error of 5%
- b, the average number of individuals to be sampled per cluster = 40 (derived from 4.85% of expected deliveries per population),

Substituting, the number of clusters needed for the survey is 18.7, implying that a minimum sample size of 748; adjusted for 10% non response we will recruit 823 participants from 21 clusters (see annex 5).

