**C=1+(Z_α/2_ + Z_β_)^2^[π_0_(1- π_0_)/n + π_1_(1- π_1_)/n + k^2^(π_0_^2^ _+_ π_1_^2^)]/ (π_0 +_ π_1_)^2^**

Substituting for n=868, we arrive at a cluster number of 8 per arm; two arms will therefore require 1,736 participants distributed between 16 health centres; implying an average of 108 pregnant women enrolled per health centre for the entire four months. This will necessitate recruiting an average of 27 pregnant women per health centre per month.

This sample is based on the following assumptions:

- A degree of error, 0.05
- (95% confidence interval, **Z_a_** =1.96),
- the power to detect a significant difference between two comparison groups of 80% (**Z_a/2_** =0.84) to detect a 10% difference;
- **π_0_**, the current prevalence of institutional deliveries 23.5% ([DHO 2010](#_ENREF_28));
- **π_1_**, expected prevalence of institutional deliveries after the intervention 33.5% and
- A design effect **D,** 2.5 and
- Coefficient of variation between clusters of the same group **k_m_,** 0.25

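### Section 4.4.8 applies the 10% loss allowance as a multiplication by 1.10, so 868 women per arm tolerate a loss of about 9%, not the stated 10%

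*Protocol*

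**What the plan says.** Section 4.4.8 sizes the trial on institutional delivery. The control rate is the "current rate of institutional deliveries, 23.5" per cent, and the other input is the "estimated rate of institutional deliveries after the intervention, 33.5" per cent. The design effect is 2.5, with normal deviates of 1.96 and 0.84. The assumptions listed after the cluster formula match these: "A degree of error, 0.05", a "95% confidence interval", and "the power to detect a significant difference between two comparison groups of 80" per cent. The stated result is 788 per arm. The next clause adds the reserve: "allowing for a 10% loss-to-follow up we estimate a total population of 868 participants per arm".

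The inflated figure is then used throughout. It is entered in the cluster formula, doubled to 1,736, turned into about 108 women per centre and 27 per centre per month, repeated as the enrolment target in section 4.4.9, and shown in the study profile in section 4.4.11.

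The two formative surveys use the same step. Section 4.2.7 starts from 120: "Considering a 10% non response we obtain a sample size of 132 health workers". Section 4.3.5 starts from 748: "adjusted for 10% non response we will recruit 823 participants from 21 clusters".

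**The concern.** A loss to follow-up is ordinarily a fraction of the women enrolled. To keep n women after losing a fraction L, a trial must enrol n/(1 − L). Multiplying by (1 + L) always gives a smaller number and so leaves fewer than n when the loss occurs. Section 4.4.8 multiplies. Its sentence names a requirement, a loss rate and an enrolment figure, and the three do not agree. No other passage gives a different loss rate or a further reserve for the trial.

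What is at stake is whether a figure used through the rest of the section supports the claim attached to it. Women are followed until four weeks after the end of pregnancy, so loss is a real planning quantity here. The printed calculation can be checked without any analysis plan.

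**Working it through.** **Inputs (section 4.4.8).** Rates 0.235 and 0.335; design effect 2.5; deviates 1.96 and 0.84, so (1.96 + 0.84)² = 7.84; loss 10%.

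**Reproducing the plan's requirement.** The variance term is 0.235 × 0.765 + 0.335 × 0.665 = 0.40255. With the squared difference of the rates in the denominator,

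n = 2.5 × 7.84 × 0.40255 / 0.10² = 789.0,

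which the protocol gives as 788. The printed denominator has a sum instead of a difference and would give about 24, so the difference was evidently used. That sign is a separate matter.

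**Reproducing 868.**
- 789 × 1.10 = 867.9, which rounds to 868, the stated figure.
- 788 × 1.10 = 866.8, which rounds to 867. The printed 868 therefore comes from the unrounded 789.

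**Checking the allowance.**
- Women left after a 10% loss: 868 × 0.90 = 781.2, which is 6.8 below 788.
- Loss that 868 can absorb: 1 − 788/868 = 9.2% (9.1% against 789).
- Enrolment that does absorb 10%: 788/0.90 = 875.6, so 876; or 789/0.90 = 876.7, so 877.

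**Power on the plan's formula, design effect held at 2.5.** Power = Φ(0.10/√(2.5 × 0.40255/n) − 1.96).

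| n per arm analysed | Power |
|---|---|
| 789 | 79.95% |
| 788 | 79.90% |
| 781 | 79.55% |

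The cost is about 0.3 percentage points.

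**Sub-study two (section 4.3.5).** The requirement is 1.96² × 0.42 × 0.58 × 2/0.05² = 748.7, stated as 748. Then 748 × 1.10 = 822.8, so 823. At 10% non-response 823 × 0.90 = 740.7, about seven below 748. The margin at 741 is 1.96 × √(0.42 × 0.58 × 2/741) = 5.03%, against the planned 5%. Dividing gives 748/0.90 = 831.1, so 832. The plan's 21 clusters at 40 women each would give 840, which is above 832.

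**Sub-study one (section 4.2.7).** The formula gives 1.96² × 0.25/0.09² = 118.6, rounded up in the protocol to 120. Then 120 × 1.10 = 132, and 132 × 0.90 = 118.8, which meets 118.6. The margin is 8.99%, within the planned 9%.

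**The case against.** **Convention.** Adding 10% to a required number is a common shorthand, and the protocol never says that the 10% is a fraction of those enrolled. Had the text said only that 10% was added, there would be little to correct. It instead claims to allow for a 10% loss, and 868 does not do that on the ordinary meaning of the words. The wording point stands.

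**Size.** The correction is finer than the inputs. The 2.5, the ten-point difference and the 10% are round planning values. The plan's own rounding is of similar size: 27 women × 4 months × 16 centres = 1,728, already eight below 1,736. This is fair, and it is why the point is minor.

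**The design effect need not stay at 2.5.** Losing women shrinks the clusters. Assume eight fixed centres per arm and a design effect of 1 + (m − 1)ρ, where m is the number of women per centre. If 2.5 refers to 788/8 = 98.5 women per centre, ρ = 1.5/97.5 = 0.0154; the design effect at 781/8 is 2.487, and power is 79.8%. If 2.5 refers to the enrolled 868/8 = 108.5, ρ = 1.5/107.5 = 0.0140; the design effect after loss is 2.35, and power is 82.0%, so there is no power deficit. The protocol does not say which cluster size its 2.5 belongs to. The shortfall in women against 788 is therefore firm, while the power loss depends on holding the design effect fixed.

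**Reach.** Because the same multiplication appears three times, a reader might infer that every stated sample size fails to deliver what it promises. The documents do not support that. In sub-study one, 132 still meets the unrounded requirement after a 10% loss, and the gap exists only against the rounded 120. In sub-study two the margin moves by about 0.03 percentage points, and the planned clusters would cover the difference. Both are descriptive surveys, so these two instances show a repeated habit and no threefold failure.

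**Conclusion.** The point holds for the trial figure and is small. At the stated 10% loss, taken as a share of women enrolled, 868 per arm leaves about 781, seven short of 788, and tolerates a loss of about 9.2%. With the design effect held at 2.5, power falls from 79.9% to 79.6%; on some readings of the design effect it does not fall below target at all. For sub-study two this is a remark only, and for sub-study one nothing follows from it.

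A reader might also infer that enrolling eight or nine more women per arm would put the sample size right. It would not. Both printed formulas carry a sum where a difference is needed. The stated eight clusters per arm do not reproduce either: with a difference in the denominator and a coefficient of variation of 0.25, the cluster formula gives about 9.6 per arm if 868 is entered, as the text describes, and about 12.1 if about 108 women per centre is entered. Those matters are separate and much larger.

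**What to change.** In section 4.4.8, restate the allowance: 868 women per arm (1,736 in total) allow for a loss to follow-up of about 9%. This changes wording only. The enrolment target, the per-centre numbers and the study profile stay as they are.

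If the sample size is revised for any other reason, divide the requirement by 0.90 so that the slip is not carried forward. On the present inputs that gives 876 per arm from 788, or 877 from the unrounded 789 (1,754 in total, about 110 per centre). Choosing this instead of the wording change would mean enrolling eight or nine more women per arm, about 1%.

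For consistency, section 4.3.5 could note that 823 allows for about 9% non-response (1 − 748/823 = 9.1%), or that 21 clusters of 40 would cover the full 10%. Section 4.2.7 needs no change.

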**C=1+(Z_α/2_ + Z_β_)^2^[π_0_(1- π_0_)/n + π_1_(1- π_1_)/n + k^2^(π_0_^2^ _+_ π_1_^2^)]/ (π_0 +_ π_1_)^2^**

Substituting for n=868, we arrive at a cluster number of 8 per arm; two arms will therefore require 1,736 participants distributed between 16 health centres; implying an average of 108 pregnant women enrolled per health centre for the entire four months. This will necessitate recruiting an average of 27 pregnant women per health centre per month.

This sample is based on the following assumptions:

- A degree of error, 0.05
- (95% confidence interval, **Z_a_** =1.96),
- the power to detect a significant difference between two comparison groups of 80% (**Z_a/2_** =0.84) to detect a 10% difference;
- **π_0_**, the current prevalence of institutional deliveries 23.5% ([DHO 2010](#_ENREF_28));
- **π_1_**, expected prevalence of institutional deliveries after the intervention 33.5% and
- A design effect **D,** 2.5 and
- Coefficient of variation between clusters of the same group **k_m_,** 0.25

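### The cluster formula in Section 4.4.8 does not give 8 health centres per arm on its own inputs, and its two clustering assumptions (k=0.25 and D=2.5) disagree, so the stated 80% power is not supported under k

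*Protocol*

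**What the plan says.** Section 4.4.8 (Sample size) works in two steps.

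- **Women per arm.** A formula with "the design effect of 2.5" and rates of 23.5% and 33.5% gives 788 women per arm, raised to 868 for 10% loss to follow-up. Here n is defined as the participants in each arm.
- **Centres per arm.** A second formula replaces D by k, with n in the binomial terms. The protocol writes "Substituting for n=868, we arrive at a cluster number of 8 per arm", and then spreads 1,736 women over 16 centres, about 108 each.

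The closing list of assumptions gives "the current prevalence of institutional deliveries 23.5"%, "expected prevalence of institutional deliveries after the intervention 33.5"%, D of 2.5, and 0.25 for the "Coefficient of variation between clusters of the same group". It claims "the power to detect a significant difference between two comparison groups of 80"% for a 10-point difference. D and k are listed together as assumptions of the same sample. The figure of 8 centres per arm is carried into Sections 4.4.5, 4.4.9 and 4.4.11.

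**The concern.** The section prints a formula, its inputs and an answer, and the three do not agree. The binomial terms stand beside a between-cluster variance term, so they describe sampling error within one centre and need the centre size. The arm total makes that error look about eight times too small.

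The number of centres largely determines what a cluster trial can detect. If 8 per arm gives clearly less than 80% power under the stated k, a non-significant result for institutional delivery could be read as evidence against a 10-point effect that the trial had only a moderate chance of finding. The section is the trial's only sample-size justification.

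**Working it through.** **Inputs**, all from Section 4.4.8: Z = 1.96 + 0.84 = 2.80, so Z² = 7.84; π0 = 0.235; π1 = 0.335; k = 0.25; D = 2.5; 868 women and 8 centres per arm; 10% loss.

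Derived quantities:
- π0(1−π0) + π1(1−π1) = 0.179775 + 0.222775 = 0.40255
- k²(π0² + π1²) = 0.0625 × 0.16745 = 0.010466
- women per centre: 868/8 = 108.5 enrolled; 788/8 = 98.5 evaluable (or 0.9 × 108.5 = 97.65)

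**1. Women per arm: reproduced.** With the squared difference in the denominator, n = 2.5 × 7.84 × 0.40255 / 0.10² = 789, against the stated 788, and 789 × 1.10 = 868. The printed denominator, (π0 + π1)², would give 24. The plus sign is therefore a misprint and the calculation used the minus sign. The minus sign is used below.

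**2. Centres per arm: not reproduced.** C = 1 + 7.84 × [0.40255/n + 0.010466] / 0.01

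| n in the formula | C | centres per arm |
| --- | --- | --- |
| 868 (as in the protocol) | 9.57 | 10 |
| 788 | 9.61 | 10 |
| 108.5 (enrolled per centre) | 12.11 | 13 |
| 98.5 (evaluable per centre) | 12.41 | 13 |

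Other readings tried for n=868: without the leading 1, C is 8.57, so 9; with the plus sign as printed, 1.26, so 2. A one-sided Z of 1.645 gives 7.75, so 8, but the protocol states 1.96. With 1.96, C=8 would need k of about 0.225 at n=868, or 0.17 to 0.18 at the real centre size.

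**3. D against k, at 108.5 women per centre.** The intracluster correlation implied by k is ρ = k²π/(1−π), and the design effect is 1 + (m−1)ρ.
- At 23.5%: ρ = 0.0192, design effect = 1 + 107.5 × 0.0192 = 3.1
- At 33.5%: ρ = 0.0315, design effect = 1 + 107.5 × 0.0315 = 4.4
- Both arms pooled: (0.003710 + 0.010466)/0.003710 = 3.8
- In reverse, D = 2.5 means ρ = 1.5/107.5 = 0.01395, so k = 0.21 at 23.5% and 0.17 at 33.5%

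**4. Power with 8 centres per arm, 23.5% against 33.5%.** Under k=0.25 the standard error of the difference is √(0.014176/8) = 0.0421 at 108.5 per centre, so the non-centrality is 0.10/0.0421 = 2.376. Under D=2.5 the variance is 2.5 × 0.40255 divided by the women per arm.

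| assumption | women analysed | t test, 14 df | normal approximation |
| --- | --- | --- | --- |
| k = 0.25 | 108.5 per centre | 60% | 66% |
| k = 0.25 | 98.5 per centre | 59% | 65% |
| D = 2.5 | 868 per arm | 78% | 84% |
| D = 2.5 | 788 per arm | 74% | 80% |

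Under k=0.25 the difference detectable with 80% power (t test) is 13.4 points at 108.5 women per centre and 13.6 at 98.5. For sensitivity, k=0.20 gives 72-73% power for 10 points and k=0.30 gives 48%.

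**The case against.** A reader might infer that the trial's power is simply 60% rather than 80%. The documents do not support that, for two reasons.

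- The 60% depends on k=0.25. The same section states D=2.5 as well, and that input produced the number of women. Under D, the normal formula used in the section returns about 80% with 788 women, and even a 14-df t test gives 74-78%. Nothing in the protocol gives k priority over D.
- The t-test figure is not the power of an analysis the protocol names. Section 4.4.10 describes chi-square tests and logistic regression. A normal approximation under k gives 65-66%.

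Both points stand, and they limit how firmly one power figure can be quoted. They do not rescue the cluster count: that step uses k, not D, and does not return 8 even with the protocol's own n. Nor do they remove the conflict, since D and k cannot both hold at this centre size.

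A reader might also count the plus sign in the denominators as a cause of the shortfall. It is not: 788 follows only from the minus sign, so the misprint changed no figure.

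**Conclusion.** The stated cluster number is wrong on its own inputs: 10 per arm with n=868, and 13 with n taken as women per centre, against 8. The two clustering assumptions are inconsistent. For 8 centres per arm, power for the 10-point difference is about 59-60% under k=0.25 and 74-78% under D=2.5 by cluster-level t test, or 65-66% and 80-84% by normal approximation. The 80% claim is thus not supported by the protocol's k, and is met under D only on the normal approximation. Which figure applies depends on which assumption the sponsor can justify. All of this assumes equal centre sizes, the minus sign in the denominators, and 98 to 108 women per centre.

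**What to change.** Revise Section 4.4.8:

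1. Define n in the cluster formula as women per health centre.
2. Choose one clustering assumption, k or D, justify it, and derive both the number of women and the number of centres from it. Substituting the pooled 3.8 for D while keeping 868 per arm would only move the conflict: 7.84 × 0.40255/0.01 × 3.82 is about 1,206 women per arm before losses.
3. Correct the stated cluster result.
4. Restate the power for 8 centres per arm with about 98 evaluable women each. If k=0.25 is kept, that is about 59% for 23.5% against 33.5%, and 80% for a difference of about 13.6 points (cluster-level t test, 14 df).
5. As a minor correction, print (π0 − π1)² in both denominators.

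The cost is protocol text only. The restatement needs no further women or centres, but under k=0.25 the declared power becomes less favourable.

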### 4.4.9 Sampling procedure

Sixteen health centres in total will be proportionally selected from both Masindi and Kiryandongo district with Masindi contributing to 10 and Kiryandongo contributing to 6 HCs. A community trail involving two arms will be tried.

*Selection of the experimental units (pregnant women)*

Ten and six health centres will be proportionally selected from Masindi and Kiryandongo district giving a total of 16 heath centres in the trail.

From the 16 selected health centres, 8 of these will be purposively assigned to each of the two arms to minimize contamination. In each of the 8 health centres on each trial arm, 868 pregnant women with 28 weeks of pregnancy or below will be enrolled as they come in giving a total of 1736 in this trial. Health centres on two extremes of the districts will be assigned to either the intervention or the control group in order to avoid contamination between the two.

*Data Collection tools and procedures*

Semi-structured questionnaires written in English but administered in Runyoro will be used by research assistants.

*Training of research assistants*

Data collectors will be recruited and trained on data collection methods for two days. Training will include how to conduct individual interviews and data collection skills

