## 1.5.2 Activity packages

Health centres are further categorised as HC II, III or IV depending on the activity package that it should deliver.

The HC II is essentially an outpatient unit with curative consultation and ambulatory care. Increasingly, however, the health centre II level provides ANC care and conducts deliveries for pregnant women and where a DHS deems it necessary they deploy a qualified midwife in addition to the other staffs. Meanwhile, the HC III is expected to provide outpatients consultations, with an inpatient bed capacity of about 15 beds. It provides laboratory diagnostics, ANC and delivery of pregnant women.

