# Chapter Four

# Study Methodology

## 4.1 Study site and population

The study will be done in the two districts of Masindi and Kiryandongo in western Uganda, 214 kilometres northwest of Kampala the capital city of Uganda. It is bordered by Amuru district in the north; Oyam to the northwest; Apac in the South; Hoima to the southwest and Bulisa in the Northwest. It is administratively divided in to three counties (Buruli, Kibanda and Bujenje); eight sub counties and 40 parishes. The district population is projected to be 603,000 inhabitants by 2010, 50.9% being male and 49.1% female. Its inhabitants are of heterogeneous ethnicity and nationality; the Banyoro comprising about 59%. The population is predominantly rural with about 5.43% being urban. It has a population density of 124 per square kilometres.

There are two general Hospitals and one sub district hospital, Masindi, Kiryandongo and Bwijanga respectively; 16 health centre III levels and; 26 health centre II levels (Masindi having 25 health centres while Kiryandongo has 17. In this region ANC new attendance is 89.4%; ANC fourth visit is 29.4%; IPT_2_ at 27.2% and Health facility deliveries in this region is 23.5% ([DHO 2010](#_ENREF_28)).

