### 4.4.11 Study profile: sub study three

Figure 6

Masindi District

Kiryandongo District

Districts

HCs

16 Health Centres (VI, III & II)

Control Arm:

8 HCs (n=**868**):

Intervention Arm

8 HCs (n=**868**):

Study Arms

Recruitment & follow-up

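### The 16 centres are chosen and assigned to arms without regard to facility level, so a level imbalance could bias the comparison of institutional delivery, by an amount the documents do not fix

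*Protocol*

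**What the plan says.** **Selection.** Protocol section 4.4.9: "Sixteen health centres in total will be proportionally selected from both Masindi and Kiryandongo district", ten from Masindi and six from Kiryandongo. District is the only stated basis.

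**Assignment.** The same section assigns eight centres to each arm purposively, using centres at opposite ends of the districts to limit contamination. Location is the only stated criterion.

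**Levels in the trial.** The study profile (4.4.11) shows "16 Health Centres (VI, III & II", so levels are mixed. Section 4.1 counts "16 health centre III levels and; 26 health centre II levels" in the two districts. Annex 10 lists 31 eligible centres by health sub-district and does not show their level.

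**What level means.** Section 1.5.2 presents level II as mainly an outpatient unit. It adds that such units increasingly give antenatal care and conduct deliveries, and that "where a DHS deems it necessary they deploy a qualified midwife in addition to the other staffs". Level III is given about 15 beds, a laboratory, antenatal care and deliveries.

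**Analysis.** Section 4.4.10 admits to the logistic model the variables that are significant in bivariate tests. Facility level is not named there or among the variables in 4.4.7.

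**The concern.** Institutional delivery is one of the primary outcomes and the one used for the sample size. The Protocol itself separates the levels partly by delivery capacity, so level is a plausible predictor of this outcome. With only eight centres per arm, moving one or two level III centres from one arm to the other changes the mix noticeably. Nothing in selection or assignment prevents this. Because assignment is purposive, there is not even a chance mechanism that would balance level on average. A centre listed in one arm cannot be moved afterwards, so this has to be settled before assignment.

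At stake is an arm difference that partly reflects the kind of facility rather than the education and phone package. The direction is unknown: it could inflate or hide an effect.

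**Working it through.** **1. The plan's own yardstick.** Inputs from section 4.4.8: "A degree of error, 0.05" (z = 1.96); "the power to detect a significant difference between two comparison groups of 80" per cent (z = 0.84); "current rate of institutional deliveries, 23.5" per cent; "estimated rate of institutional deliveries after the intervention, 33.5" per cent; design effect 2.5. With the difference of the two rates in the denominator (the printed formula has a plus sign, which would give about 24):

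n = 2.5 × (1.96 + 0.84)² × [0.235 × 0.765 + 0.335 × 0.665] / 0.10² = 2.5 × 7.84 × 0.40255 / 0.01 = 789 per arm (stated 788).

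789 × 1.10 = 867.9, the stated 868. The figure reproduces, and the target difference is 10 points.

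**2. Level mix (assumption).** If the 16 centres mirrored the counts in section 4.1, 16 × 16/42 = 6.1, so about 6 level III and 10 level II. The mix of the 31 centres in Annex 10 is not given.

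**3. How uneven a split could be.** For orientation only, a random 8/8 split of 16 centres with 6 at level III is hypergeometric:

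| Level III split | Probability |
|---|---|
| 3:3 | 39.2% |
| 4:2 either way | 49.0% |
| 5:1 either way | 11.2% |
| 6:0 either way | 0.7% |

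So 61% of random splits would be uneven. The actual assignment is purposive, so these are not this trial's probabilities.

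**4. Shift in the arm difference.** With equal enrolment per centre, shift = (difference in number of level III centres / 8) × (level III rate minus level II rate). The rate gap is an assumption, shown as a range:

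| Split | Factor | Gap 10 | Gap 20 | Gap 30 |
|---|---|---|---|---|
| 4:2 | 2/8 | 2.5 | 5 | 7.5 |
| 5:1 | 4/8 | 5 | 10 | 15 |

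**5. A bound from the plan's own k.** Section 4.4.8 sets the between-centre coefficient of variation at 0.25. At the control rate the between-centre SD is 0.25 × 23.5 = 5.9 points. If level were the only source of that variation, with a level III share of 16/42, the gap would be 5.875 / √(0.381 × 0.619) = 12.1 points. Then 4:2 gives 12.1 × 2/8 = 3.0 points and 5:1 gives 12.1 × 4/8 = 6.0 points. Even 6:0 gives 12.1 × 6/8 = 9.1 points.

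**6. What such a shift does to the test.** With no true effect and the planned design effect, the effective size is 788/2.5 = 315.2 per arm and the standard error is √(2 × 0.235 × 0.765 / 315.2) = 0.0338. A fixed shift of 3, 5 or 6 points would then be declared significant about 14%, 32% or 43% of the time, instead of 5%.

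**The case against.** The strongest reply is that the contrast between levels may be small. Section 1.5.2 says level II units increasingly conduct deliveries, section 1.5.1 puts antenatal and delivery services in the health centres' minimum package, and section 1.5.3 says the intervention seeks centres that give both. The operational definitions count delivery in any formal facility, so a woman enrolled at a level II unit who delivers at a level III unit or a hospital is still a success. All of this stands, and it softens the contrast. It does not remove it: the remark in 1.5.3 is background and not a selection rule in 4.4.9, and centres that all conduct deliveries can still differ in beds, laboratory and midwife cover.

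The two-level calculation also leaves things out. The study profile shows a third level, and Annex 10 lists Bwijanga, which section 4.1 calls a sub-district hospital. The 6:10 mix is therefore only illustrative.

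A reader might infer three stronger things that the documents do not support:

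- That the levels differ in whether they do deliveries at all. Section 1.5.2 says otherwise; the supported difference is in capacity.
- That imbalance alone would produce half or all of the 10-point target. All of it needs, for example, a 5:1 split together with a 20-point gap, and no rate by level is given. Under the planned k and 6 level III centres, even complete separation stays below 10 points.
- That level adds variation on top of k = 0.25. As defined in 4.4.8, k covers all variation between centres of the same group, so level is already inside it.

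Finally, a statistical analysis plan might name level as a covariate. That could help the model, but it would not change which centres are in which arm, and section 4.4.10 already states a rule that leaves adjustment to bivariate significance.

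**Conclusion.** The point holds as a conditional risk. Selection by district and purposive assignment by location leave facility level uncontrolled, in a trial sized on institutional delivery whose own text gives the levels different delivery capacity.

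The most defensible size is the one tied to the plan's k: about 3 points for a 4:2 split and about 6 for a 5:1 split, against a 10-point target. These figures are close to an upper bound under that k, because they let level explain all of the variation between centres. The larger entries in the table (gaps of 20 or 30 points) would require more between-centre variation than the plan assumes. Everything rests on an assumed mix of 6 level III centres in 16, equal enrolment per centre and an assumed rate gap. If the eligible level II units deliver care much as level III units do, the bias could be negligible. The correction is worth making because it is cheap and is only available before assignment.

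**What to change.** 1. Add a column for facility level to Annex 10, and reconcile the levels shown there with sections 4.1 and 4.4.11.
2. In section 4.4.9, select and assign centres so that, within each district, the arms have the same number of centres of each level or differ by at most one. Where both districts have an odd number of a level, let the surplus go to opposite arms. Balanced numbers remove the level shift. One surplus centre leaves gap/8, that is 1.25 points at an assumed 10-point gap and 2.5 points at 20.
3. In section 4.4.10, name facility level as an adjustment term in the arm comparison, whatever its bivariate p-value.

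The cost is a re-listing of centres before the start, slightly less freedom to pick centres far apart (and so a little more care over contamination), and one or two degrees of freedom with 16 clusters.
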